# **Statistical Analysis Plan: Healthy behaviours, cardiovascular disease and all-cause mortality in the UK Biobank**

## **Aims**

To investigate the association between adherence to healthy behaviours and the risk of total cardiovascular disease (CVD), fatal CVD and total mortality by BMI group in the UK Biobank.

## **Outcomes**

The main outcomes are incidence of any form of CVD, fatal CVD, and total mortality. Incident cardiovascular disease will be defined as a hospital admission or death with ICD-10 (international classification of diseases, 10th revision) codes including: coronary heart disease (CHD; I20-I25, K49, K50, K75, K40-K46), congestive heart failure or cardiomyopathy (CHF; I50, I50.1, 150.9, I11.0, I13.0, I13.2, I42, I43.1), and total stroke (I60-I64). For total fatal CVD events, we will use I00-I25, I27-I88, and I95-I99. Total mortalities will be obtained from death registries.

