## **Exclusions /Inclusions**

List of exclusions:

- Pregnancy
- BMI <18.5 kg/m^2^.
- Participants who have a diagnosis of CVD at baseline. This includes the outcome variables of coronary heart disease, congestive heart failure, cardiomyopathy and stroke.

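### The CHD outcome is labelled ICD-10 but lists K codes that ICD-10 assigns to digestive disease or leaves unassigned, so total CVD is wrong as written

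*SAP*

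**What the plan says.** The SAP's Outcomes section names three main outcomes: any CVD, fatal CVD and total mortality. Any CVD is a "hospital admission or death with ICD-10 (international classification of diseases, 10th revision) codes including" three groups of conditions. The first group is "coronary heart disease (CHD; I20-I25, K49, K50, K75, K40-K46". The others are heart failure or cardiomyopathy, and "total stroke (I60-I64". ICD-10 is the only classification named, and it governs the whole list. The SAP mentions no procedure classification and no procedure field.

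Fatal CVD has its own list: "For total fatal CVD events, we will use I00-I25, I27-I88, and I95-I99". Total mortality is taken from death registries.

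The Exclusions /Inclusions section removes people with CVD at baseline and adds: "This includes the outcome variables of coronary heart disease, congestive heart failure, cardiomyopathy and stroke". It gives no codes and no data source for prevalent disease.

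**The concern.** The K codes do not fit the coding system that the sentence names. ICD-10 chapter K covers digestive disease, so a programmer who follows the text would count a hernia repair admission or a Crohn's disease admission as coronary heart disease. If the K codes are meant as procedure codes, the same programmer would not look for them in procedure data. The definition would then gain false events and lose intended ones.

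Total CVD is an outcome in the primary and secondary analyses and in the supplementary analysis of metabolic health. The event indicator also fixes the event age. The Stata command given under the Cox model timescale uses one exit age and one failure indicator per person, so a false first event would end follow-up and hide a later true one.

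**Working it through.** The SAP gives no event counts or rates, so there is no planned figure to reproduce. The check compares the code lists with the named classification and with each other, and then shows how dilution would work under stated assumptions.

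**1. Codes against the named system.** These meanings come from ICD-10, which the SAP invokes, and not from text in the SAP.

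| Code in the CHD list | Meaning in ICD-10 | Effect of a literal search |
|---|---|---|
| I20-I25 | Ischaemic heart disease | Correct events |
| K40-K46 | Hernias | False events |
| K50 | Crohn's disease | False events |
| K75 | Inflammatory liver diseases | False events |
| K49 | Unassigned | No matches |

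**2. Lists against each other.** The stroke and fatal CVD lists contain only I codes. The I codes in the incident list all fall inside the fatal list: I11.0, I13.0, I13.2 and I20-I25 lie in I00-I25, and I42, I43.1, I50 and I60-I64 lie in I27-I88. The K codes fall outside it. A death coded K50 would therefore count as incident CVD but not as fatal CVD. (The entry 150.9 in the heart failure list looks like a slip for I50.9.)

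**3. Which outcomes are reached.** Total CVD is reached directly. The definitions of fatal CVD and total mortality contain no K code, so neither gains false events. If the baseline exclusion uses the same list, people with earlier hernia, Crohn's or liver disease leave the cohort, and all three outcomes are then affected.

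**4. Illustration of dilution.** Let f be the share of total-CVD events in the reference group (four healthy behaviours) that are false, and let HR be the true hazard ratio. Assume false events occur at the same rate in every behaviour group. With reference rate r:

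- reference: (1 − f)r + fr = r
- exposed: (1 − f)r × HR + fr
- observed ratio: (1 − f) × HR + f

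For example, with HR = 1.50 and f = 0.20, the result is 0.80 × 1.50 + 0.20 = 1.40.

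| Assumed f | True HR 1.30 | True HR 1.50 | True HR 2.00 |
|---|---|---|---|
| 10% | 1.27 | 1.45 | 1.90 |
| 20% | 1.24 | 1.40 | 1.80 |
| 30% | 1.21 | 1.35 | 1.70 |
| 40% | 1.18 | 1.30 | 1.60 |

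If false events do vary with behaviours, with their own ratio g, the last term becomes f × g and the bias need not be towards 1.

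**5. BMI strata.** The secondary models interact behaviours with BMI group. If f differed between strata, say 10% in one and 30% in another (assumed), a constant true HR of 1.50 would appear as 1.45 and 1.35. The coding alone would then produce a ratio of 1.35/1.45 = 0.93 between strata.

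**The case against.** The strongest reply is that only a label is missing. The list is headed coronary heart disease, so a search for hernias would contradict its own heading. A reader who knows hospital data would probably take the K codes as coronary revascularisation procedures and search the procedure field. On that reading the intended outcome is sound and no false events arise. This is fair as an account of what was probably meant, and it makes the harm conditional on how the codes are run. It does not rescue the text, because nothing in the SAP sends the K codes to a procedure field. An analyst who does so is applying a definition that the plan does not contain.

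A reader might also infer several stronger claims that the document does not support:

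- **That every hazard ratio is diluted.** Only total CVD is affected directly.
- **That the wrong people are certainly removed at baseline.** The exclusion refers to the outcome variables but gives no codes, so reuse of the list is a plausible reading and not a stated rule.
- **That all the K codes are digestive diagnoses.** K49 is unassigned.
- **That the codes are known to be OPCS-4.** The SAP never mentions that classification, so this is an inference.
- **That the bias is of a known size, or differs by BMI because hernia is related to BMI.** The SAP supports neither the 10% to 40% range nor any BMI gradient in false events.

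**Conclusion.** The definition is wrong as written and must be fixed. It is a faulty rule for a main outcome, not detail left to another document. That conclusion needs only the SAP's own ICD-10 label and the standard meaning of the codes under it.

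The consequence depends on execution. If the list is run literally on diagnosis and death fields, total CVD takes in non-cardiovascular events and captures no revascularisation procedures. Total-CVD hazard ratios are then distorted, and move towards 1 if the false events are unrelated to behaviours. The extent cannot be estimated from the SAP, and the dilution figures show only how the error would act. Fatal CVD and total mortality are affected only if the baseline exclusion uses the same code list.

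**What to change.** In the Outcomes section:

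- Restrict the ICD-10 definition of CHD to I20-I25, applied to the diagnosis and death fields.
- State that no ICD-10 K code counts as CVD.
- Have the authors confirm that K40-K46, K49, K50 and K75 are procedure codes, name the classification, and apply them only to the operative-procedure field.

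In the Exclusions /Inclusions section, state that the same split definition identifies CVD at baseline.

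The cost is a sentence or two of SAP wording and a search of two kinds of field instead of one. No new data collection is needed. If event files have already been derived, check which fields the K codes were run against.

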## **Exposures**

Four healthy behaviours will be classed as exposures all measured at cohort inception from a questionnaire administered then. These will be analysed separately and then as a total number of healthy behaviours. No data to estimate change in these variables is available:

1. *Smoking status.* This will be classified as “Never”, “Current” and “Previous” as per smoking status self-reported by the UK Biobank participants. Being a never smoker is defined as a healthy behaviour.
2. *Alcohol intake frequency*. To be divided into “None”, “Occasional” (<1 unit/ week), “Moderate” (1-14 units/ week) and “Heavy” (>14 units/ week). A healthy behaviour for this study is defined as ‘none’ or ‘occasional’ alcohol intake. Data was calculated from participants’ responses to estimate consumption of red wine^†^; champagne and white wine ^†^; beer and cider^†^; spirits^†^; fortified wine^†^.
3. *Fruit and Vegetable Score.* The sum of the following variables was calculated: Fresh fruit intake^†^, raw vegetable intake^†^, cooked vegetable intake. These were summed and a healthy behaviour defined as 5 or more servings of fruit and vegetables a day.
4. *Physical Activity.* Derived MET score from number of days/week of vigorous physical activity 10+ minutes^†^; Duration of vigorous activity; number of days/week of moderate physical activity 10+ minutes^†^; duration of moderate activity and number of days/week walked 10+ minutes^†^; duration of walks ^†.^ A healthy behaviour was defined as 150 or more minutes of moderate activity, or 75 minutes or more of vigorous activity a week, or a combination of the two, as defined by the UK CMO physical activity guidelines.

**BMI**

Participants will be stratified into four BMI categories as follows; BMI 18.5 -24.9, 25-29.9, 30-34.9 and >=35 kg/m^2^. The category 18.5-24.9 kg/m^2^will be the reference group.

## **Exclusions /Inclusions**

List of exclusions:

- Pregnancy
- BMI <18.5 kg/m^2^.
- Participants who have a diagnosis of CVD at baseline. This includes the outcome variables of coronary heart disease, congestive heart failure, cardiomyopathy and stroke.

## **Covariates & Effect Modifiers**

### 1. Specific coding of covariates

Population demographics:

- Age: time underlying time co-variate in the Cox model.
- Ethnicity: White, Black, Asian, Other
- Townsend score (quintiles 1-5, with lower score representing greater affluence)
- Education: categorical (1: higher degree, 2: any school degree, 3: vocational qualifications, 0: none of the above)
- Sex (Male:0; Female: 1)
- Region of UK

Health factors:

- Family history of diabetes (No:0; Yes: 1)
- Family history of CVD (No:0; Yes: 1)
- Menopausal status (men:0, premenopausal women: 1, postmenopausal women:2)

## 2. Plan for dealing with missing data

- Participants with missing data in key variables will be dropped:
  - If the exposure measurements smoking status, alcohol intake, fruit and vegetable score, physical activity score were missing or unknown.
  - Other key confounders in the model: Townsend score, education, age, sex, region of UK, family history of diabetes or hypertension, if missing, we will create a category called “Unknown”
  - If menopausal status is missing, age >=55 will be used as a proxy.
  - If key stratification variable BMI was missing or unknown.

## **Planned main analyses**

## 1. *Descriptive statistics*

For continuous variables: mean, standard deviation

For categorical variables: 2 x k tables, frequency distributions

## *2. Multivariable analysis*

*PRIMARY ANALYSIS*: to investigate the association between number of healthy behaviours and the total CVD events, fatal CVD and total mortality overall using sex and region stratified models

### *SECONDARY ANALYSIS:* to investigate the association between number of healthy behaviours and the risk of total CVD events, fatal CVD and total mortality in the 4 BMI strata using sex and region stratified models

For both the primary and secondary analysis the number of healthy behaviours (0,1,2,3 or 4) out of a total of 4 will be used as the main exposure, using 4 as the reference category

### For both the primary and secondary analysis:

1. Timescale for the Cox model:

Time from inception to incident of disease will be represented by age. We will use the following command in Stata before the model: stset age_out, id(ID) fail(outcome) enter(age_in)

1. Adjustment:

We will use a multivariable confounding model adjusted for: Age, Townsend score, education, sex, region of UK, family history of diabetes or hypertension and menopausal status.

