**In summary:**

*Primary analysis*

1. CVD = #beh + BMI + cova

*Secondary analysis*

1. CVD= #behaviours*BMI group + covariates
2. CVD= individual behaviours*BMI group + covariates

*Supplementary analysis*

1. CVD=#behaviours*BMI group*Metabolic Conditions + covariates

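### The plan codes ethnicity and family history of CVD as covariates, but the stated Cox adjustment set names neither and uses an uncoded family history of hypertension, so the plan supports two different main models

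*SAP*

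**What the plan says.** Under Specific coding of covariates, the SAP gives coding for "Ethnicity: White, Black, Asian, Other". It also gives two family-history items, "Family history of diabetes (No:0; Yes: 1") and "Family history of CVD (No:0; Yes: 1"). Age, Townsend score, education, sex, region and menopausal status complete that list.

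The adjustment step that governs both the primary and the secondary analysis says the models are "adjusted for: Age, Townsend score, education, sex, region of UK, family history of diabetes or hypertension and menopausal status".

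The missing-data section describes its own list as the confounders in the model: "Other key confounders in the model: Townsend score, education, age, sex, region of UK, family history of diabetes or hypertension". These receive an Unknown category when missing, and menopausal status has its own proxy rule based on age.

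The primary analysis is to be run "overall using sex and region stratified models". The closing summary writes the first secondary model as "CVD= #behaviours*BMI group + covariates" and does not itemise the covariates.

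**The concern.** In an observational cohort, adjustment is the main protection against confounding, so the SAP has to fix the adjustment set before the models are fitted. Here the list of coded covariates and the list of model covariates disagree, and no reason is given.

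The two variables left out are ones the plan itself names as covariates, and both could plausibly matter.

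- **Ethnicity.** The alcohol item gives a healthy point for no intake or occasional intake. Alcohol, smoking and diet may differ by ethnic group. The group with four healthy behaviours, which is the reference for every contrast, may therefore differ in ethnic mix from the others. If the mix also differs across BMI strata, the comparison of strata could be affected.
- **Family history of CVD.** Of the family-history items, this is the closest to two of the three outcomes, total CVD and fatal CVD.

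There is also a practical consequence. If either variable is added later, the plan does not say what happens to participants for whom it is missing.

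**Working it through.** The plan gives no figure to reproduce on this point, so the check is a comparison of the three lists.

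| Variable | Coding section | Missing-data section | Adjustment step |
|---|---|---|---|
| Age | yes | yes | yes |
| Townsend score | yes | yes | yes |
| Education | yes | yes | yes |
| Sex | yes | yes | yes |
| Region | yes | yes | yes |
| Family history of diabetes | yes, on its own | yes, joined with hypertension | yes, joined with hypertension |
| Menopausal status | yes | yes, own rule | yes |
| Ethnicity | yes | no | no |
| Family history of CVD | yes | no | no |
| Family history of hypertension | no | yes | yes |

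**Counts.** The coding section has 9 variables. The adjustment step has 8 if diabetes and hypertension are counted separately. They share 7. So 9 − 7 = 2 are coded but not in the model (ethnicity, family history of CVD), and 8 − 7 = 1 is in the model but not coded (family history of hypertension). The missing-data set equals the adjustment set.

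**If hypertension is a slip for CVD.** All 8 model variables are then coded, and 9 − 8 = 1 is left out: ethnicity.

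**Does another section settle it?** The summary does not itemise its covariates. Stratification is by sex and region only. The coding section's heading also mentions effect modifiers, but no interaction with ethnicity is planned.

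**Scale, for illustration only.** For a single binary confounder, the observed hazard ratio for 0 against 4 behaviours is roughly the true one multiplied by

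B = [1 + p0(RR − 1)] / [1 + p4(RR − 1)],

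where p0 and p4 are the confounder's prevalence in the two groups and RR is its relation to the outcome. Every input below is assumed; none is in the SAP.

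| Confounder | p4 | p0 | RR | B |
|---|---|---|---|---|
| Ethnic group | 10% | 3% | 1.5 | 1.015/1.05 = 0.967 |
| Ethnic group | 15% | 4% | 1.5 | 1.02/1.075 = 0.949 |
| Ethnic group | 20% | 4% | 2.0 | 1.04/1.20 = 0.867 |
| Ethnic group | 15% | 4% | 0.7 | 0.988/0.955 = 1.035 |
| Family history | 50% | 50% | any | 1.000 |
| Family history | 50% | 60% | 1.3 | 1.18/1.15 = 1.026 |
| Family history | 50% | 60% | 2.0 | 1.60/1.50 = 1.067 |

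The factor falls on both sides of 1. The formula is for a crude association. Townsend score, education and region are already in the model and may absorb part of any ethnic difference.

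**The case against.** The best defence is that nothing has been shown to be omitted. The summary models adjust for covariates, and the section that bears that name includes ethnicity and family history of CVD. An analyst who read those two parts together would adjust for both. This stands as far as it goes: the documents establish that two adjustment sets are possible, not that the analysis will leave the variables out. It does not remove the problem. The adjustment step is the more specific text, it expressly governs both analyses, and the missing-data section agrees with it.

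Secondly, hypertension may be a slip for CVD, since the coding section has exactly two family-history items, diabetes and CVD. That is possible and the text cannot settle it. The term occurs in two sections, so it is not a single typing error. Even on this reading, ethnicity is still absent from the model and from the missing-data rule.

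Thirdly, family history of hypertension is not wholly unmentioned: the missing-data section names it. That is correct. What it lacks is coding, and it is unclear whether diabetes or hypertension means one combined variable or two.

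Finally, a reader might infer that the hazard ratios are understated by a definite percentage. The documents do not support that. They give no distribution of behaviours or risk by ethnic group, four ethnic categories and three outcomes are involved, and a group at lower risk reverses the direction.

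**Conclusion.** The inconsistency is real and lies in the specification of the main models. As written, the explicit model omits ethnicity and family history of CVD, both of which the plan codes as covariates, and includes a family-history item that it does not code. If hypertension stands for CVD, the omission reduces to ethnicity alone.

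The hazard ratios from the explicit model would be open to avoidable confounding. Its size and direction are unknown. The illustrative factors of about 0.87 to 1.07 rest wholly on assumed prevalences and relative risks and on a crude, one-confounder formula; they are not an estimate for this cohort. It would go too far to say that every hazard ratio is confounded, or that the behaviour effect is understated.

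This is more than a missing detail, because it allows two different primary models. It should be settled before the main models are fitted.

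**What to change.** - Use one covariate list in the coding section, the missing-data section, the adjustment step and the summary.
- Add ethnicity and family history of CVD to the adjustment step. If the sponsor means to leave either out, the plan should say so and give the reason.
- Extend the Unknown category rule to both variables.
- Either code family history of hypertension in the coding section, stating whether it is separate from or combined with diabetes, or replace or delete it in the missing-data section and the adjustment step.

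**Cost.** A wording change to the SAP and a few model terms. Ethnicity with an Unknown level has 5 levels, so 4 terms. Family history of CVD with an Unknown level has 3 levels, so 2 terms. That is at most 6 extra terms, and the loss of precision should be negligible in a cohort of this kind. Both variables are already coded in the plan.

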## **Sensitivity analyses**

- Removing the first 2 years of follow up to try to limit the potential for reverse causality

## **Supplementary analyses**

Some research has suggested that it is possible to have obesity and be ‘metabolically healthy’. In this study ‘metabolically healthy’ will be defined as those participants without a diagnosis of hypertension, diabetes or high cholesterol. We will explore the following questions:

1. How prevalent is ‘metabolically healthy’ status amongst participants who have obesity?
   - We will determine the % of the population with BMI>30 with and without metabolic complications
2. Does ‘metabolically healthy’ obesity lower the incidence of total CVD, fatal CVD and total mortality compared to ‘non-metabolically healthy’ obesity? How does the incidence of total CVD, fatal CVD and total mortality in ‘metabolically healthy’ obesity category compare to the incidence of total CVD, fatal CVD and total mortality in the ‘normal’ BMI category?
   - We will re-run our models (Secondary analyses) to have an interaction between BMI with presence/absence of metabolic complications

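### 'Metabolically healthy' rests only on the absence of a diagnosis but is read as the absence of disease, so undiagnosed disease overstates its prevalence and can bias the question 2 contrasts

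*SAP*

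**What the plan says.** The SAP section on supplementary analyses defines the 'metabolically healthy' as "participants without a diagnosis of hypertension, diabetes or high cholesterol". It gives no measured value, no medication criterion, and no source or date for the diagnosis.

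The same indicator serves two questions:

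- **Question 1 (prevalence):** "We will determine the % of the population with BMI>30 with and without metabolic complications".
- **Question 2 (outcomes):** whether metabolically healthy obesity would "lower the incidence of total CVD, fatal CVD and total mortality compared to" its unhealthy counterpart, and how it compares with the 'normal' BMI category. The secondary models are re-run "to have an interaction between BMI with presence/absence of metabolic complications".

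The closing summary lists the model as "CVD=#behaviours*BMI group*Metabolic Conditions + covariates".

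The only sensitivity analysis is "Removing the first 2 years of follow up to try to limit the potential for reverse causality". The missing-data section gives no rule for metabolic status.

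**The concern.** Having no diagnosis is not the same as having no condition: a diagnosis requires that someone was tested. The rule therefore partly measures contact with health care, whereas the wording of both questions and the name of the model term read it as metabolic state.

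People with undiagnosed disease fall into the healthy group. Question 1 then counts too many as healthy. In question 2 the healthy-obesity group may carry risk that belongs to the unhealthy group. The study might then report that metabolic health makes little difference in obesity, or that healthy obesity carries excess risk over normal BMI, when part of either result comes from misclassification.

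Nothing in the plan would reveal this. Dropping the first two years of follow-up leaves everyone's metabolic label unchanged. Adjusting for Townsend score and education does not correct a mislabelled exposure.

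**Working it through.** The SAP states no prevalence, undiagnosed share or effect size for this analysis, so there is no planned figure to reproduce. Every input below is an assumption, chosen to show direction and range.

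**Notation, among people with obesity**

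- p = true share metabolically healthy
- u = share of truly affected people who are undiagnosed
- R = true rate ratio, unhealthy versus healthy
- Diagnoses are taken to have no false positives. Undiagnosed people are first given the same risk as diagnosed people.

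**Formulas**

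- Labelled prevalence = p + (1 − p)u
- Affected share of the labelled-healthy group: c = (1 − p)u / [p + (1 − p)u]
- Observed unhealthy-versus-healthy ratio = R / [1 + c(R − 1)]
- Observed healthy-obesity ratio against the whole normal-BMI group = true ratio × [1 + c(R − 1)]
- If the comparator is normal BMI without a diagnosis, divide the last line by [1 + cₙ(R − 1)], where cₙ is the affected share of that comparator.

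**Results for p = 0.40, R = 2.0 and a true ratio against normal BMI of 1.20.** The last column assumes that 75% of the normal-BMI group is truly healthy, with the same u.

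| u | Labelled prevalence | c | R = 2.0 appears as | 1.20 appears as, whole normal-BMI group | 1.20 appears as, normal BMI without a diagnosis |
|---|---|---|---|---|---|
| 0.1 | 0.40 + 0.06 = 46% | 0.06/0.46 = 0.130 | 2/1.130 = 1.77 | 1.36 | 1.31 |
| 0.2 | 0.40 + 0.12 = 52% | 0.12/0.52 = 0.231 | 2/1.231 = 1.62 | 1.48 | 1.39 |
| 0.4 | 0.40 + 0.24 = 64% | 0.24/0.64 = 0.375 | 2/1.375 = 1.45 | 1.65 | 1.48 |

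With p from 0.2 to 0.6 and u from 0.1 to 0.4, prevalence is overstated by (1 − p)u, that is by 4 to 32 percentage points. A true ratio of 2.0 appears as 1.24 to 1.88, and a true 1.5 as 1.15 to 1.45.

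**Does attenuation always follow?** No. Let 60% be diagnosed with hazard 1.8 relative to the truly healthy. Of the 40% labelled healthy, let a tenth (4% of all) be undiagnosed with hazard 1.2. The true unhealthy-versus-healthy ratio is (0.60 × 1.8 + 0.04 × 1.2)/0.64 = 1.128/0.64 = 1.76. The observed ratio is 1.8/(1 + 0.1 × 0.2) = 1.8/1.02 = 1.76. There is no attenuation, because the missing low-risk cases would also have lowered the unhealthy group's average.

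**Does the upward bias against normal BMI always follow?** No. If the comparator is limited to people without a diagnosis and has the same affected share and relative hazard as the healthy-obesity group, the two factors cancel exactly. With unequal shares, as in the last column, part of the bias remains.

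**The case against.** The definition is stated openly. The SAP puts the term in quotation marks, says what it means in this study and presents the questions as exploratory. Only the supplementary analysis uses the variable; the primary and secondary analyses do not. Measured blood pressure, glucose, cholesterol and medication data appear nowhere in the document, so whether they can be used is unknown. All of this stands, and it limits the weight of the point. It does not remove it: the questions and the model term still speak of complications and conditions rather than diagnoses, and no limitation is stated.

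Three stronger readings are tempting, and the document supports none of them.

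- **That the healthy-versus-unhealthy contrast must be pulled towards 1, perhaps almost abolished.** The check above shows a case with no attenuation. A fall from 1.8 to 1.20 (1.8/1.50) would need half of the labelled-healthy group to be affected, with a hazard of 2.0 against 1.8 in diagnosed people. Nothing in the SAP supports undiagnosed people faring worse than diagnosed ones.
- **That the excess over normal BMI must be inflated.** The question names the normal-BMI category as a whole, but an interaction with metabolic status also splits that category. The SAP does not say which comparison will be reported.
- **That treated people without a recorded diagnosis are counted as healthy.** The SAP does not describe how a diagnosis is ascertained, so medication use may or may not contribute to it.

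**Conclusion.** The point holds in conditional form. If some affected participants are undiagnosed and false-positive diagnoses are negligible, the question 1 prevalence is overstated. Attenuation of the healthy-versus-unhealthy obesity contrast further requires that undiagnosed people carry risk materially above the truly healthy and similar to the diagnosed. Upward bias against normal BMI depends on the comparator, which the SAP leaves unclear.

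No single size can be given from the SAP. The tabulated figures are illustrations and estimate nothing about this cohort. They do show that the error could be large enough to change how the supplementary results are read. The change should be made, but it is not critical to the main conclusions.

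**What to change.** In the supplementary analyses section and the matching line of the closing summary:

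1. Pre-specify a second version of the metabolic variable. It counts as affected anyone with a diagnosis, use of a relevant medicine, or a baseline blood pressure, glucose/HbA1c or cholesterol measurement above a pre-stated cut, where the resource holds these data (an assumption).
2. Report questions 1 and 2 under both this version and the diagnosis-only version.
3. State whether the normal-BMI comparator is the whole category or only those without metabolic disease under the same definition.
4. If the data are not held, label the group 'obesity without diagnosed metabolic disease' and restrict the conclusion to that.

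The cost is SAP wording and the derivation of one further variable from baseline data. Some participants will lack measurements, and the healthy-obesity group becomes smaller under the broader definition. The fallback in step 4 needs wording only.

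### The model written out for the metabolically healthy obesity question adjusts for smoking only through one point of the behaviour count, leaving residual smoking confounding of unknown size and direction below a count of 4

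*SAP*

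**What the plan says.** Question 2 under Supplementary analyses asks how metabolically healthy obesity compares with metabolically unhealthy obesity, and with the normal BMI category, for total CVD, fatal CVD and total mortality. The stated method is: "We will re-run our models (Secondary analyses) to have an interaction between BMI with presence/absence of metabolic complications".

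The closing summary gives one supplementary model: "CVD=#behaviours*BMI group*Metabolic Conditions + covariates". Two models are listed there as secondary: one with the behaviour count, and "CVD= individual behaviours*BMI group + covariates". The second has no counterpart under the supplementary heading.

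The count is defined under Secondary analysis: "the number of healthy behaviours (0,1,2,3 or 4) out of a total of 4 will be used as the main exposure", with 4 as the reference category. Under Exposures, smoking is recorded in three classes (never, current, previous), but only one earns the point: "Being a never smoker is defined as a healthy behaviour". The adjustment set is "Age, Townsend score, education, sex, region of UK, family history of diabetes or hypertension and menopausal status", which names none of the four behaviours. The only sensitivity analysis drops the first two years of follow-up.

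**The concern.** In the primary and secondary analyses the behaviour count is the exposure. In question 2 it is not: the groups compared are defined by BMI and metabolic status, and behaviours are things to adjust for. Adjusting for a sum does not balance its parts. A current smoker with good diet and activity, a former smoker with the same habits, and an inactive never smoker with otherwise the same habits can share a count. If one BMI group tends to lose its point through smoking and another through inactivity, equal counts stand for unequal risk. Scoring current and previous smokers alike adds to this, because two groups with the same share of ever smokers can differ in the share who still smoke.

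At stake is the reading of question 2. A bias of several percent could shift how metabolically healthy obesity is described relative to normal BMI, and no analysis listed for the supplementary question would show that this had happened.

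**Working it through.** **What the text fixes.** The SAP states no figure on this point, so there is none to reproduce. Read together, the summary model, the adjustment list and the scoring of smoking mean that, in the supplementary model as written, smoking acts only through the count.

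**Illustration.** All inputs below are assumptions; none comes from the SAP. Two groups, normal BMI (N) and metabolically healthy obesity (O), have a true hazard ratio of 1 given behaviours. Each is split into 24 cells: smoking (3) × alcohol (2) × fruit and vegetables (2) × activity (2), independent within group. In rows A to F the healthy level is met by 30% for alcohol, 35% for fruit and vegetables, and 55% (N) or 40% (O) for activity. Hazard ratios for missing it are 1.0, 1.2 and 1.3.

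*Count 0, by hand.* Everyone has missed the other three behaviours, so those factors cancel. Let c be the current share of ever smokers.

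ratio = [c_O·HR_cur + (1−c_O)·HR_prev] / [c_N·HR_cur + (1−c_N)·HR_prev]

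- Row A (c = 0.30 in N, 0.20 in O; HR 2.5 and 1.3): (0.50 + 1.04)/(0.75 + 0.91) = 1.54/1.66 = 0.928.
- Row E (c = 0.25 and 0.30): 1.66/(0.625 + 0.975) = 1.66/1.60 = 1.038.

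*Count 1, with identical smoking in both groups (row F).* The never-smoker share at this count still differs, because activity differs.

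- N: never smokers 0.55×0.70×0.65×0.45 = 0.1126; ever smokers with exactly one other healthy behaviour 0.45×(0.0878 + 0.1103 + 0.2503) = 0.2017; share 0.1126/0.3143 = 36%.
- O: never smokers 0.55×0.70×0.65×0.60 = 0.1502; ever smokers 0.45×(0.117 + 0.147 + 0.182) = 0.2007; share 0.1502/0.3509 = 43%.

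*Averaged over counts.* With n_k the group's weight at count k and h_k its weight times hazard, the Mantel-Haenszel-type ratio is

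Σ h_Ok·n_Nk/(n_Nk+n_Ok) ÷ Σ h_Nk·n_Ok/(n_Nk+n_Ok).

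| Row | N: never/previous/current % | O: never/previous/current % | HR current, previous | Count 0 | 1 | 2 | 3 | 4 | Averaged |
|---|---|---|---|---|---|---|---|---|---|
| A | 55/31.5/13.5 | 55/36/9 | 2.5, 1.3 | 0.928 | 0.948 | 0.979 | 0.996 | 1.000 | 0.961 |
| B | 58/29.4/12.6 | 50/40/10 | 2.5, 1.3 | 0.928 | 0.968 | 1.002 | 1.011 | 1.000 | 0.978 |
| C | as B | as B | 1.8, 1.15 | 0.952 | 0.985 | 1.009 | 1.012 | 1.000 | 0.991 |
| D | 58/27.3/14.7 | 50/42.5/7.5 | 3.0, 1.3 | 0.821 | 0.888 | 0.952 | 0.988 | 1.000 | 0.909 |
| E | 58/31.5/10.5 | 50/35/15 | 2.5, 1.3 | 1.038 | 1.045 | 1.050 | 1.032 | 1.000 | 1.043 |
| F | 55/33.75/11.25 | same as N | 2.5, 1.3 | 1.000 | 0.997 | 1.008 | 1.010 | 1.000 | 1.003 |
| G | 54/30/16 | 54/40/6 | 3.0, 1.4 | 0.822 | 0.851 | 0.910 | 0.961 | 1.000 | 0.883 |

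Row G also sets activity met at 60% (N) and 45% (O), with hazard ratios of 1.1 for low fruit and vegetables and 1.2 for inactivity. A Poisson rate model with group and five-level count gave the same averaged values to within 0.001. Replacing the count by separate terms for the four behaviours returned 1.00 in every row, as it must when the effects are multiplicative. The small departures at counts 2 and 3 partly reflect the unequal effects of the other behaviours.

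**Scale.** If the true ratio were 1.15 (assumed), the two ends would report 1.15 × 0.88 = 1.01 and 1.15 × 1.04 = 1.20.

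**The case against.** Four points count against a strong form of this.

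- **The planned model is a three-way interaction, not a main-effects adjustment.** With count 4 as reference, its BMI and metabolic terms are contrasts among people who meet all four behaviours, hence never smokers. Smoking status cannot confound them, as the count 4 column shows. A reader might infer that the whole of question 2 is left confounded; the documents do not support that. What remains is counts 0 to 3 and any averaged contrast. Question 2 asks about whole categories, and the SAP does not say which contrast will be reported.
- **The text speaks of secondary models in the plural.** Re-running the individual-behaviours model with metabolic status would carry smoking as its own term. So the SAP does not clearly decide to omit it. But the summary lists only the count version, and nothing says whether the individual behaviours would enter jointly.
- **Direction.** A reader might infer that metabolically healthy obesity will look too benign. That needs more current smoking in the normal BMI group at a given count. The SAP gives no such figures, and row E goes the other way.
- **Coverage.** Only obesity versus normal BMI was calculated. The same mechanism could act between metabolically healthy and unhealthy obesity, but no size is shown for it.

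It also stands that the count adjusts partly for smoking, and that this is an exploratory question which touches neither the primary nor the secondary analysis.

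**Conclusion.** The point holds as one of residual confounding. As written out, the question 2 model controls smoking only through an unweighted count point that merges current with previous smokers. At counts 0 to 3, and in any average over counts, the contrast is open to smoking differences of unknown size and direction; at count 4 it is not.

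The range of about 0.88 to 1.04 for the averaged ratio, and 0.82 to 1.05 at single counts, rests wholly on assumed frequencies and effects. It shows that several percent is possible, not that it will occur: with identical smoking in both groups (row F) the averaged ratio was 1.003. Because the analysis is supplementary, this is a change the sponsor should make, not one on which the main results depend.

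**What to change.** Keep the planned interaction of count, BMI group and metabolic conditions as the look at whether the behaviour gradient differs by metabolic status. Nothing here argues for deleting it.

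For the two question 2 contrasts (metabolically healthy obesity versus unhealthy obesity, and versus normal BMI), add to the supplementary list, and report:

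outcome = BMI group × metabolic conditions + smoking (never/previous/current) + alcohol (four classes) + fruit and vegetables + physical activity + covariates, with the behaviours entered jointly.

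The wording under Supplementary analyses and the summary list should then name the same models.

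**Cost.** One extra model for each of the three outcomes. The behaviours take 2 + 3 + 1 + 1 = 7 degrees of freedom, against 4 for a five-level count. In total the added model has (4×2 − 1) + 7 = 14 such terms, fewer than the 5×4×2 − 1 = 39 of the full three-way interaction. No new data are needed: the behaviours are already collected and classed, and participants missing any of them are already dropped under the missing-data plan.
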